### Subgroup analysis

We will also do some exploratory subgroup analyses based on the following characteristics:High vs. low baseline adherenceHigh vs. low baseline intrinsic motivation to take treatmentHigh vs. low baseline self-efficacyHigh vs. low frequency in usage of sending and receiving messages through their mobile phone

### Standard errors

We will estimate Huber-White robust standard errors in all analyses. All standard errors will be clustered at the individual level.

### Adjusting for multiple hypotheses

*P*-values will be adjusted for multiple hypothesis testing for all secondary outcomes by applying a false discovery rate adjustment (FDR) following Benjamini et al. (2006) [42]. In particular, we will use the sharpened *q*-values discussed in Anderson (2008) [43]. This correction will control for the expected proportion of type 1 errors.

### Data management

Existing clinic identifiers will be used as unique study identification numbers during data collection. Consent forms will bear the name and signatures of study participants, but all other information (such as viral load tests and Wisepill measurements) will be collected using these unique clinic identifiers. The study team in Uganda (one team leader, two lead interviews, and three supporting team members) will be in charge of collecting all of the data and carrying out the in-person intervention. All survey data will be collected with computer-assisted software (SurveyCTO) using a tablet. The survey data will be uploaded to the password-protected study computer at the end of each day (at which point they are then automatically deleted from the device) and saved in an encrypted folder on that computer.

All datasets and files with identifiers will always remain encrypted through a zipped folder or by using BoxCryptor within DropBox, an online data portal that can only be accessed using a secure password. Adherence to HIV antiretrovirals will be monitored using a Wisepill device. Data from these devices will be uploaded remotely to an encrypted server using a sim card embedded in the Wisepill device in real time. Participant adherence data will then be downloaded and stored securely via BoxCryptor and will only be identified via an alpha-numeric clinic ID. SMS messaging data will be downloaded from the messaging platform, Telerivet. Text messaging data will not include sensitive or private information, such as the participant’s name or current HIV status at any point. Downloaded datasets will include text messages sent and received, time, and date of messages. For any data exports containing participant’s phone number, we will ensure this always remains in an encrypted folder using BoxCryptor within DropBox.

Paper copies of consent forms will be stored and locked at the Mildmay RAND office in Kampala, and access will only be granted to key personnel and the study PIs. Any published material will not contain participants’ identifying information. There is no formal data monitoring committee since the trial was deemed minimal risk, but data monitoring will occur through weekly checks by the study team in the USA, and an independent study monitor.

### Handling missing data and attrition

Missing data have been a minor issue in our previous studies with the same study population and outcomes. Attrition has been well under 10% per year. However, when subjects drop out, we will fit multiple logistic regression models to assess whether this dropout is random. If it is not, we will construct “nonresponse” weights using logistic regression that correct for dropout by assigning weights to continuing subjects that are inversely proportional to the predicted probability of the subjects’ continuing to the time period in question. Analyses will incorporate design effects from this weighting in the calculation of standard errors and tests of significance. In addition, we will present sensitivity tests regarding changes in outcomes when excluding those with missing observations to give a fully transparent picture of the data.

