### Sampling and participants

We expect to enroll 1256 individuals for the observation phase of the study that serves to measure baseline adherence. Monitoring baseline adherence will ensure that individuals being randomized to the interventions are indeed those in need of adherence support, i.e., have relatively low baseline mean adherence of less than 90%.

We arrived at this starting sample size in the following way. For the primary outcome of adherence, a sample size of 140 participants in each arm (*n* = 560 total) will be able to detect an 8 percentage point (pp) difference in mean adherence between each treatment arm and control, and compared to each other. The corresponding difference at month 24 is 9 pp. This assumes mean control group adherence of 62%. In order to reach this required sample size at year 3, we assume 6% attrition per year over 2 years of the study (1.06^2 = 1.1236) which results in a sample size for the beginning of GOALS recruitment to be 629 (560 × 1.1236). To ensure an even number across the four study arms, we reduce this target from 629 to 628. We then assume that 50% of those who complete the adherence observation phase are eligible for the GOALS intervention. We therefore need a starting sample size of 1256 ((628/50) × 100). All assumptions surrounding attrition rates and rates of adherence are based on data from PI [name]’s previous study at the same site.

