### Retention

To promote participant retention and complete follow-up, the study has aligned its activities with the participants’ clinic visit dates. By doing this, the study aims to ensure that participants are not only coming to the clinic for study-related activities but also for their routine clinical visits. This approach is expected to reduce the burden on participants, minimize missed appointments, and increase compliance with the study protocol. Participants who discontinue the study will return their Wisepill devices and we will not be collecting outcomes data.

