### Data analysis

Our primary analyses will be intention-to-treat analyses, with secondary analyses involving study completers only.

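### Dropout weights are used only if an unspecified check finds dropout non-random; the bias this adds is small, but unconditional weighting that uses adherence up to dropout would be better

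*Protocol article*

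**What the plan says.** Under Handling missing data and attrition, the protocol article sets a two-stage rule. First, "we will fit multiple logistic regression models to assess whether this dropout is random". Second, "If it is not, we will construct" nonresponse weights that are "inversely proportional to the predicted probability of the subjects’ continuing to the time period in question". It gives no criterion for calling dropout random, and no correction for the case where it is so called. The only other analysis named there is "we will present sensitivity tests regarding changes in outcomes when excluding those with missing observations".

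Three other statements bear on this:

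- Retention: "Participants who discontinue the study will return their Wisepill devices and we will not be collecting outcomes data".
- Data analysis: "Our primary analyses will be intention-to-treat analyses, with secondary analyses involving study completers only".
- Estimating impact on primary outcomes: the unadjusted and the adjusted equation both contain strata fixed effects, and the improvement phase is analysed only on the month leading up to month 12. According to Randomization, the strata are four bands of baseline adherence.

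**The concern.** Failing to find a pattern in dropout does not show that dropout is random, least of all with few dropouts. Under the stated rule, such a failure switches the correction off. Because nothing is collected after discontinuation, and the month-12 analysis uses one late month, anyone who leaves earlier contributes nothing to that result. With the weights off, the intention-to-treat estimate is in effect an estimate among those who continued. The planned sensitivity analysis, which excludes those with missing data, then largely repeats it.

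Informative dropout is plausible here, though not shown. The Background reports that low adherers who failed to win under a 90% threshold felt demotivated, and the arms differ in how often that will happen. The stake is a comparison that flatters whichever arm loses more of its low adherers.

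**Working it through.** **1. The plan's own figure.** Sampling and participants says "we assume 6% attrition per year over 2 years of the study" and inflates 560 accordingly: 560 × 1.06² = 629.2, given as 629 and reduced to 628, or 157 per arm. This reproduces.

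**2. Number of dropouts.** Sampling and participants uses 6% a year, and Sample size and power uses 10%. Taking both as a range:

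- Month 12: 628 × 0.06 = 37.7 and 628 × 0.10 = 62.8, so about 38 to 63 over four arms.
- Two years: 628 × (1 − 0.94²) = 73.1 and 628 × (1 − 0.90²) = 119.3, so about 73 to 119.

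Month 12 is the relevant horizon for the improvement phase.

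**3. Power to see a difference in dropout rate between two arms of 157.** With a two-sided 0.05 level (assumed; the article states none), power = Φ{[|p₁ − p₂| − 1.96√(2p̄(1 − p̄)/157)] / √([p₁(1 − p₁) + p₂(1 − p₂)]/157)}. For 6% against 12%, this is Φ{(0.060 − 0.0633)/0.0321} = Φ(−0.10) = 46%.

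| Dropout rates | Power |
|---|---|
| 6% v 10% | 26% |
| 6% v 12% | 46% |
| 10% v 15% | 27% |
| 10% v 18% | 53% |

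**4. Outcome SD.** The article states none. Solving back from 8 pp, 140 per arm, 80% power and two-sided 0.05: 8 / [(1.960 + 0.842) × √(2/140)] = 23.9 pp, rounded to 24.

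**5. Bias by simulation.** Assumptions:

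- Four arms of 157, SD 24 pp and no true effect.
- Correlation 0.6 between baseline and year-1 adherence, and 0.8 between year-1 adherence and the outcome.
- Dropout in the incentive arms driven by year-1 adherence, with an odds ratio of 1.5 to 2 per SD lower.
- Strata effects in the outcome model, as planned.
- The same covariates in the check and in the weights.

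With adherence to date in the dropout model, and 6% to 10% dropout, the check misses the informative dropout in about 3% to 71% of trials. Misses are most frequent at the lower dropout and the weaker association.

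| Dropout model | Bias, check then weight | Bias, always weight |
|---|---|---|
| Arm, baseline adherence, adherence to date | about 0.2 pp or less (6% to 10% dropout) | about 0 |
| Arm and baseline adherence only | about 0.4 to 1.6 pp | about 0.4 to 1.6 pp |

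In the second row, the lower values belong to month-12 dropout and the higher to two-year dropout. Reading down the table, the covariates matter more than the conditional step. Always weighting with adherence to date cost no precision in these runs.

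**6. Scale.** The standard error implied by 8 pp at 80% power is 8/2.802 = 2.86 pp. A bias of 0.2 pp is 0.2/2.86 = 0.07 standard errors; 1 pp is 0.35 and 2 pp is 0.70.

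**7. What weights cannot reach.** In a two-arm run at roughly 12% to 14% dropout, dropout depended on the part of the outcome not explained by baseline adherence, and the dropout model held only arm and baseline terms. The check flagged 5% to 11% of trials, and the bias was 1.3 to 2.6 pp with or without weights.

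**The case against.** The case against has five parts.

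- **No test is named.** The article speaks of an assessment, without a p-value or threshold, so every power figure above rests on an assumed 0.05 level. That is true. A yes-or-no decision is still built into the rule, and leaving its criterion open makes the choice of estimator more discretionary, not less. The covariates and threshold may be in an analysis plan that is not shown, so their absence is not the point. The point is the stated rule, which such a plan would inherit.
- **The planned model already absorbs much of the bias.** This stands. In runs where dropout was driven by baseline adherence, bias of 0.5 to 1.9 pp without strata effects fell to about 0 to 0.25 pp with them and no weights.
- **The conditional step is not the main source of bias.** This also stands. A reader might infer that the step alone costs 1 to 2 pp. That size appears only if the check is denied the variable that drives dropout while the weights are given it, if strata effects are ignored, or if two-year dropout is applied to a month-12 analysis. The article does not restrict the dropout model to baseline variables, so it does not support that reading. With matched covariates and 12% to 19% dropout, another set of runs put the bias left after check-then-weight at about 0.1 to 0.4 pp.
- **Differential loss is conjecture.** The article gives no dropout by arm, reports attrition well below 10% a year in earlier work, and plans to carry the weighting into the standard errors. All of this is fair, and it limits the severity.
- **Always weighting is not a cure.** A reader might infer that removing the step deals with informative dropout in general. It does not: item 7 of the working shows bias that no weighting on measured variables removes.

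**Conclusion.** The point holds at low severity. The article states a conditional rule that would often leave informative dropout uncorrected at month 12, and the section offers no unconditional weighted or imputed analysis. The bias due to the conditional step itself is about 0.2 pp or less at 6% to 10% dropout, small beside 8 pp. Putting adherence up to dropout in the model is worth more: up to about 1 pp at month 12 and 2 pp at two years. These sizes rest on the assumed SD, correlations, odds ratios and 0.05 cut-off. It would go too far to say that the rule invalidates the intention-to-treat analysis. It is a weak choice with a nearly free replacement.

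**What to change.** Delete the conditional step. Prespecify inverse-probability weights or multiple imputation for the primary analysis whatever any check of dropout shows. The dropout or imputation model should contain arm, baseline adherence, Wisepill adherence to date and arm-by-adherence terms; the continuous Wisepill record up to discontinuation makes this feasible. Report the unweighted complete-case result as a sensitivity analysis. Add a not-at-random sensitivity analysis, because weights correct only for measured predictors of dropout.

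The cost is a change of wording, slightly more analysis work and possibly slightly wider intervals. No data collection or sample size changes.

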It remains an open question how best to deliver incentives to improve health behaviors. In existing interventions, incentives typically reward individuals for reaching a certain performance goal, commonly a high threshold set uniformly for all individuals, such as a physical activity milestone [19], adherence of 90% [10], or viral suppression [20]. However, people differ in their levels of baseline performance and capacity to improve their performance. Because traditional, high uniform goals do not reward marginal improvements, they consequently reward those with already healthy behaviors. Individuals who are far from such a high threshold must exert great effort to reach it—and yet any marginal improvements they make will not be rewarded, leading to demotivation. For behaviors which require repeated actions such as (daily) adherence, this structure can discourage effort over time, leading to no or only minimal improvement among those not capable of immediately reaching the high goal. In our own studies, adherence improvements were driven by those with already relatively high initial adherence of about 60–80%. Those with adherence below this level did not benefit from our incentive intervention that set the eligibility threshold at 90% mean adherence, and reported that failing to win the incentives caused demotivation [10]. Adolescents and young adults have the lowest levels of self-esteem of any age group [21] and are therefore particularly susceptible to demotivation. Redesigning incentives to enable those (youth) with low baseline adherence to reach their goals is thus of paramount importance.

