### Intervention modifications

Participants will be discontinued from the study if they experience serious adverse events related to the intervention. Participants will also be discontinued from the study at their own request, if they are not in a position to adhere to study protocols which include the use of Wisepill devices to monitor their medication intake.

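### Every stated missing-data analysis uses only participants who stayed, so the named sensitivity test cannot show whether the arm contrasts withstand dropout related to adherence

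*Protocol article*

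**What the plan says.** All references are to the protocol article.

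- **Data analysis:** "Our primary analyses will be intention-to-treat analyses, with secondary analyses involving study completers only".
- **Handling missing data and attrition:** when subjects drop out, "we will fit multiple logistic regression models to assess whether this dropout is random". If dropout is judged not random, the plan corrects by "assigning weights to continuing subjects that are inversely proportional to the predicted probability of the subjects’ continuing to the time period in question". It then adds that "we will present sensitivity tests regarding changes in outcomes when excluding those with missing observations". No other missing-data sensitivity test is named.
- **Intervention modifications:** besides serious adverse events related to the intervention, discontinuation follows when the participant asks for it, and the condition given is "if they are not in a position to adhere to study protocols which include the use of Wisepill devices to monitor their medication intake".
- **Retention:** "Participants who discontinue the study will return their Wisepill devices and we will not be collecting outcomes data".
- **Outcomes, Primary outcome:** mean adherence is doses taken over doses prescribed, from device openings.
- **Data analysis, Estimating impact on primary outcomes:** the improvement phase is judged on the month before month 12 only.

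**The concern.** The main analysis is meant to compare the arms as randomised. A participant who stops using the device and asks to leave before month 12 has no value in the window that decides the improvement-phase result. If that participant's adherence would have been low, the value is missing because of what it would have been.

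None of the stated analyses varies what leavers' adherence might have been. Weighting balances stayers and leavers on recorded predictors only. The completers analysis and the exclusion test drop leavers. Where weighting is not triggered and the leaver has no month-12 value, the exclusion test is the main analysis run again, and its agreement with the main result carries no information.

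At stake are each incentive arm's contrast with control, and the contrasts of assigned (T1) and participatory (T2) subgoals with the fixed goal (T3). If low adherers left one arm more often than another, the stayers' contrast would be off in a direction that the planned check cannot detect.

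**Working it through.** **Inputs from the article.** Control mean adherence 62%, detectable difference 8 pp, 140 per arm, 80% power, two-tailed, attrition 10% a year with 8% seen in the pilot (Sample size and power). Attrition 6% a year (Sampling and participants). 157 randomised per arm (Abstract).

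**Assumptions.** Alpha 0.05. Leavers' adherence and the split of dropout by arm are illustrative, because the article gives neither.

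**The plan's own figures.** 560 × 1.06² = 629.2, matching the stated 629. No SD is given. 8 pp with 140 per arm implies SD = 8 / [(1.960 + 0.842) × √(2/140)] ≈ 23.9 pp. With that SD and 140 × 0.9² = 113.4 per arm, the detectable difference is 8.9 pp, consistent with the stated 9 pp at month 24. None of these figures is in dispute.

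**Effect of dropout on the contrast.** Let stayer means be 70% (treatment) and 62% (control). Let pT and pC be the proportions lost, and let leavers' adherence be a fraction f of their own arm's stayer mean. Then

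all-randomised contrast = 70 × [1 − (1 − f)pT] − 62 × [1 − (1 − f)pC].

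| Loss, treatment / control | Leavers at 0 (f = 0) | Leavers at half (f = 0.5) |
|---|---|---|
| 8% / 8% | 64.40 − 57.04 = 7.36 pp | 67.20 − 59.52 = 7.68 pp |
| 6% / 10% | 65.80 − 55.80 = 10.00 pp | 67.90 − 58.90 = 9.00 pp |
| 10% / 6% | 63.00 − 58.28 = 4.72 pp | 66.50 − 60.14 = 6.36 pp |

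The exclusion test reports 8 pp in every cell. With equal loss the error is 0.64 or 0.32 pp. With the illustrative split it is 2.0 or 3.3 pp (leavers at 0), and 1.0 or 1.6 pp (leavers at half).

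**What a tipping-point analysis would report.** Suppose only treatment-arm leavers fall D pp below their arm's stayers, while control leavers resemble control stayers. The contrast is then 8 − D × pT. With SD 23.9 pp and 157 × (1 − p) per arm contributing:

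- 6% loss: SE ≈ 2.78, so significance is lost at D ≈ (8 − 1.96 × 2.78)/0.06 ≈ 42 pp, that is, leavers at about 28% adherence.
- 10% loss: SE ≈ 2.84, so D ≈ (8 − 1.96 × 2.84)/0.10 ≈ 24 pp, that is, leavers at about 46%.

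If loss and shortfall in pp are the same in both arms, the contrast stays at 8 pp.

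**The case against.** The strongest reply is that this is a condensed article. The analysis plan is not shown, it may contain further sensitivity analyses, and the article does not say that its list is exhaustive. That limits the point to what the article fixes: it names a test, and that test cannot answer the question that dropout raises here.

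Weighting also deserves credit. If earlier recorded adherence enters the weight model, dropout that it predicts can be corrected. What remains is dropout linked to adherence that was never recorded.

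Four stronger readings are tempting, and the documents do not support them:

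- **That the exclusion test always repeats the main analysis.** When weights are applied, it compares weighted with unweighted stayers. The outcome is indexed by week, and the later phases are analysed over the months spent in them, so partial data can also make the two differ.
- **That low adherers are turned into missing values.** Discontinuation is at the participant's own request. Someone who stays enrolled without opening the device is scored low, not missing. The run-in also screens out people unable to use the device.
- **That the article itself predicts arm-related dropout.** Background says participants "reported that failing to win the incentives caused demotivation". That concerns motivation, not leaving the study. The 6% and 10% rates are alternative overall planning figures, and assigning one to each arm is only an illustration.
- **That a gap of two leavers per 157 always shifts the contrast by 0.8 pp.** That holds only without background attrition. At 8% background with leavers at 0, two extra control leavers give 70 × 0.92 − 62 × 0.9073 ≈ 8.15 pp, an error of 0.15 pp.

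Scoring leavers at 0 equates a returned device with no treatment taken, so it serves as a bound and not as an estimate.

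**Conclusion.** The point holds in limited form. Every missing-data analysis stated in the article conditions on staying, and the device-measured month-12 outcome is missing for anyone who left earlier. The named sensitivity test therefore cannot show whether the arm contrasts withstand outcome-related dropout.

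The numerical effect is small if arms lose similar numbers of similar people: about 0.3 to 0.6 pp of an 8 pp contrast at 8% loss. It becomes material, up to 3.3 pp in the illustration, only if loss or leavers' shortfall differs by arm. That difference is an assumption, plausible because only three arms are rewarded for recorded adherence, but nowhere stated. The figures also rest on the 62% and 70% stayer means; the tipping-point values rest in addition on alpha 0.05 and an SD back-calculated from the plan. No bias is demonstrated. What is shown is that the planned check could not detect one.

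**What to change.** Keep the exclusion test, since it gives a weighted-versus-unweighted comparison when weights are used. Add to Handling missing data and attrition a sensitivity analysis over all randomised participants, in which missing month-12 adherence is set to the arm's predicted value minus a stepped amount. Vary that amount separately by arm until the conclusion changes, with leavers at 0% as the extreme bound. Report it for each incentive arm versus control, and for T1 and T2 versus T3.

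The cost is wording and code, with no new data collection. The downside is a little more analysis work and a possibly wider reported range around each effect.
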